#### Demographic characteristics

Data at baseline and post-intervention will be described using means and standard deviations for normally distributed continuous variables, medians and interquartile ranges for non-normally distributed continuous variables, and numbers and percentages for non-continuous variables.

#### Primary and secondary outcomes

The effectiveness of the In Balance intervention in comparison with a control group will be analysed with multilevel mixed model regression analyses for both primary and secondary outcomes. Three hierarchical levels will be included in the mixed models; therapist, participant and time. If necessary, analyses will be adjusted for confounders and stratified for the presence of potential effect modifiers. The primary effect in these analyses is described by the coefficient of the time treatment interaction term. To identify possible differences in intervention effects between non-frail and pre-frail respondents, an a priori subgroup analysis will be performed, stratified for frailty level (non- and pre-frail).

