### Control group

The control group will receive written general physical activity recommendations in the form of a flyer. This flyer contains advice on physical activity levels, strength and balance for older adults. For example, a minimal amount of 150 min of moderate to vigorous physical activity per week is recommended, distributed over several days. Also muscle and bone strengthening activities such as walking stairs and balance exercises at least twice per week are advised. Moreover, the health benefits associated with physical activity are explained. These recommendations follow the Dutch Guidelines for Physical Activity [40]. To minimize study attrition, participants of both the intervention and control group will receive regular newsletters during the study and a personal advise on (changes in) physical performance after ending of the study.

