### Sample size

To obtain a reduction of 50% in the number of falls between the intervention and control group, a minimum of 106 persons are required per group, at a power of 0.80, beta of 0.02 and alpha of 0.05. Taking into account a dropout rate of 20%, the total required sample size is 256 participants. Hence, we expect that about 16 In Balance intervention groups of 8 participants each, are needed to include the required sample size of 128 participants in both the intervention and control group.

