#### Economic evaluation

For the economic evaluation, missing cost and effect data will be imputed using multiple imputation according to the algorithm developed by van Buuren et al. [63]. Linear regression analyses will be used to estimate cost and effect differences between the intervention group and the control group while adjusting for confounders if necessary. Bias-corrected accelerated bootstrapping with 5000 replications will be used to estimate statistical uncertainty surrounding the cost and effect differences. Incremental cost-effectiveness ratios (ICERs) will be calculated by dividing the difference in costs between the groups by the difference in effects. Bootstrapped cost-effect pairs will be plotted on cost-effectiveness planes to show the uncertainty surrounding the ICER. Cost-effectiveness acceptability curves will be estimated to show the probability that the In Balance intervention is cost-effective compared to control for different willingness-to-pay values (i.e. the amount of money that society is willing to pay per additional unit of effect).

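### The therapist level in the mixed model does not fit controls who have no therapist, and the economic evaluation names no such level: specify a partially nested model for both and state power over an ICC range

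*Protocol article*

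**What the plan says.** All references are to the Protocol article.

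- **Primary and secondary outcomes:** "Three hierarchical levels will be included in the mixed models; therapist, participant and time". The primary effect is the time-by-treatment coefficient. The text does not say how controls enter the therapist level.
- **Control group:** "The control group will receive written general physical activity recommendations in the form of a flyer".
- **Recruitment, randomization, blinding and treatment allocation:** individuals are randomized in blocks of 10, and therapists are told the names only of those allocated to In Balance.
- **Sample size:** the target is a halving of falls, for which the section says that "a minimum of 106 persons are required per group". Power is given as 0.80, alpha as 0.05 and beta as 0.02. After dropout the total is 256, and the section expects "about 16 In Balance intervention groups of 8 participants each". It mentions no ICC and no design effect.
- **Economic evaluation:** "Linear regression analyses will be used to estimate cost and effect differences between the intervention group and the control group", with a BCa bootstrap of 5000 replications. It names no therapist or group level and no cluster resampling.

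**The concern.** A therapist, participant, time hierarchy needs a therapist for every participant. Here only one arm has therapists, so the control arm must be coded in some way, and the choice matters:

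- If all controls form one cluster, that cluster coincides with the control condition and is confounded with treatment.
- If each control is attached to a local therapist, the random effect becomes a shared area effect. It largely cancels from the treatment contrast and misses the variation in delivery.
- If controls are singletons with no arm-specific term, one therapist variance is imposed on both arms.

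The standard error of the primary effect is thus left to a coding choice. The adjacent economic section, on the same participants, names no such level at all. Confidence intervals, cost-effectiveness planes and acceptability curves could then look more certain than the data allow. The stated power also shows no allowance for the correlation that the mixed model is built to handle.

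**Working it through.** **1. The plan's own figures.** The total reproduces: 106 × 1.20 = 127.2, rounded up to 128 per arm, 256 in all. The 106 cannot be derived, because no control fall rate, dispersion or test is given. If 1/3 versus 1/6 fallers is assumed (two proportions, two-sided 0.05, power 0.80, no clustering), n is 105 per arm; at 33% versus 16.5% it is 107. This suggests an unclustered calculation but does not prove it, since inputs to a count model can also be chosen to give about 106. I take 106 analysed per arm as 80% power at ICC 0, two-sided. The stated beta conflicts with that power; that is a separate matter.

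**2. Formulas.** With clusters of size m in the intervention arm only and equal variances in the arms:

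- DE = 1 + (m − 1) × ICC, intervention arm only
- variance factor of the contrast: f = (1 + DE)/2
- power = Φ((1.960 + 0.842)/√f − 1.960)
- proportion by which an unclustered standard error is too small = 1 − 1/√f
- n per arm for 80% power = 106 × f

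**3. Results for m = 8** (group size from the plan; the ICCs are assumptions):

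| ICC | DE | f | Power at 106 per arm | n per arm | Unclustered SE too small by |
|---|---|---|---|---|---|
| 0 | 1.00 | 1.000 | 80.0% | 106 | 0% |
| 0.01 | 1.07 | 1.035 | 78.6% | 110 | 1.7% |
| 0.02 | 1.14 | 1.070 | 77.3% | 114 | 3.3% |
| 0.05 | 1.35 | 1.175 | 73.4% | 125 | 7.7% |
| 0.10 | 1.70 | 1.350 | 67.4% | 144 | 13.9% |

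**4. Sensitivity to cluster size.** With 106 analysed in 16 groups, m = 106/16 = 6.6, and power is 78.9%, 77.8% and 74.6% at ICC 0.01, 0.02 and 0.05. If one therapist led two groups (m = 16, which the documents do not state), it would be 77.1%, 74.3% and 66.6%.

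**5. Economic intervals.** Coverage of a nominal 95% interval that ignores the clustering is 2Φ(1.96/√f) − 1. For m = 8 this is 94.2%, 92.9% and 90.8% at ICC 0.02, 0.05 and 0.10.

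**6. Dependence on coding, illustrated.** Take a simple contrast of arm means, ICC 0.05, 106 per arm and unit total variance. The variance in units of 1/106 is:

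- controls independent: 1 + 1.35 = 2.35
- all controls as one cluster: (1 + 105 × 0.05) + 1.35 = 6.25 + 1.35 = 7.60, a standard error √(7.60/2.35) = 1.80 times as large
- controls shared evenly across the same therapists, random intercept only: 0.95 + 0.95 = 1.90, a standard error √(1.90/2.35) = 0.90 times as large

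These are model-based values at fixed variance components. They show that the coding matters and are not a forecast for this trial.

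**The case against.** The strongest reply is that a journal article condenses. The coding of a random effect and the resampling unit of a bootstrap are commonly left to the full protocol or SAP, which are not shown. The sentence on levels does not say that controls have a therapist. Singletons, a treatment-only random effect or linkage to a local therapist are all compatible with it. Local linkage is plausible, since therapists help to recruit and assessments take place in the participant's municipality. This stands in part: one cannot say that the trial will code controls wrongly. But the article does commit every mixed model to a hierarchy that cannot be applied literally to a control arm without therapists, and it describes a different structure for costs.

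A reader might infer more than the documents support:

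- **That the plan acknowledges a design effect.** It does not. The 16 groups of 8 are a logistic count.
- **That the sample size is shown to assume independence.** No allowance is visible, but 106 cannot be derived from the stated inputs.
- **That power and intervals are misstated as a matter of fact.** This holds only if the ICC is above zero. At 0.01 with groups of 8 the power loss is 1.4 points.
- **That the whole shortfall from 80% is due to clustering.** 128 less 20% leaves 102.4 per arm, and Φ(2.802 × √(102.4/106) − 1.960) = 78.6% already at ICC 0. That part comes from the dropout arithmetic.

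Applying the design effect to both arms would also overcorrect: 106 × 1.35 gives 144 per arm at ICC 0.05, against 125.

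**Conclusion.** The point holds in limited form. The stated three-level structure does not fit an arm without therapists, and the economic methods as named do not carry the clustering that the effectiveness model includes. Both follow from the text. The numerical consequences are conditional on an ICC that the documents do not give, on equal variances, and on groups of 8. On those assumptions the power loss is about 1 to 7 points for ICCs of 0.01 to 0.05, and economic standard errors are about 3% to 14% too small for ICCs of 0.02 to 0.10. The loss may be small. This is a should-fix: the effect on the results is likely modest, but the structure ought to be settled before data are seen because the standard error of the primary effect depends on it.

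**What to change.** - **Mixed models:** specify a partially nested model, with a therapist or course-group random effect for intervention participants only and controls as independent individuals, allowing arm-specific residual variance where the outcome model has one. State whether the cluster is the therapist, the course group or both. Let the random effect act on the term that carries the treatment effect, here time by treatment, because a therapist intercept constant over time drops out of a linear change contrast.
- **Economic evaluation:** use the same structure, with cluster-aware regression and a bootstrap that resamples course groups in the intervention arm and individuals in the control arm.
- **Sample size:** state the power over an assumed ICC range, with the design effect in the intervention arm only, and give the number of groups expected per therapist.

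The cost is analysis wording and a restated power figure. Intervals become slightly wider and the stated power slightly lower. Randomization, data collection and the intervention do not change.

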**Methods:**

This study is a single-blinded, multicenter randomized controlled trial. The target sample will consist of 256 community-dwelling non-frail and pre-frail adults of 65 years or older with an increased risk of falls. The intervention group receives the In Balance intervention as it is currently widely implemented in Dutch healthcare, which includes an educational component and physical exercises. The physical exercises are based on Tai Chi principles and focus on balance and strength. The control group receives general written physical activity recommendations. Primary outcomes are the number of falls and fall-related injuries over 12 months follow-up. Secondary outcomes consist of physical performance measures, physical activity, confidence, health status, quality of life, process evaluation and societal costs. Mixed model analyses will be conducted for both primary and secondary outcomes and will be stratified for non-frail and pre-frail adults.

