### Recruitment, randomization, blinding and treatment allocation

Recruitment will be done via flyers, advertisements in local papers, folders distributed through supermarkets, pharmacists, community centres, general practitioners, at annual flu shots, and via personal invitations by In Balance therapists and general practitioners. Participants will be randomized into the intervention group or the control group using block-randomization to balance the size of the two groups. Randomization will be stratified according to frailty. We aim to include 30–50% of the participants in the pre-frail subgroup and 50–70% in the non-frail subgroup in both the intervention and control group. As soon as one of the subgroups starts to outnumber the other subgroup, we will only target the underrepresented subgroup for recruitment. Two hundred fifty-six sealed envelopes in blocks of 10 (5 envelopes per group) will be prepared by an independent investigator. These sequentially numbered envelopes contain a random computer-generated unique identification number. A second matching envelope contains the group information. All investigators and assessors involved in this study will be blinded to group assignment until completion of statistical analyses. Due to the nature of this study, participants and therapists cannot be blinded to group allocation. Participants will be informed orally about their allocation and therapists will receive the names of those participants who will participate in the In Balance intervention.

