##### Participant characteristics

Demographic characteristics will be determined at M0 and M12, including age, sex, height, weight, marital status, living situation, work, smoking, fall history, use of walking aids, experience with fall prevention interventions, walking, balance, physical activity, use of medication and presence of chronic diseases.

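### Adjustment and effect-modifier stratification of the primary analysis depend on an undefined need, so the primary estimate is not fixed in advance; the randomisation stratum and baseline fall history are not named in the overall model

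*Protocol article*

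**What the plan says.** Under Primary and secondary outcomes, the protocol article fixes two features of the model. The first is its levels: "Three hierarchical levels will be included in the mixed models; therapist, participant and time". The second is the effect parameter: "The primary effect in these analyses is described by the coefficient of the time treatment interaction term". Between these it sets a conditional rule: "If necessary, analyses will be adjusted for confounders and stratified for the presence of potential effect modifiers". The Economic evaluation section applies the same condition to the cost and effect regressions, "while adjusting for confounders if necessary". Neither section defines when adjustment is needed, lists candidate confounders or modifiers, or says which resulting estimate is the primary one.

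Frailty appears in three places. Under Recruitment, randomization, blinding and treatment allocation: "Randomization will be stratified according to frailty". Under Primary and secondary outcomes: "an a priori subgroup analysis will be performed, stratified for frailty level (non- and pre-frail"). In the Methods paragraph of the Abstract, the mixed models for primary and secondary outcomes "will be stratified for non-frail and pre-frail adults". None of these says that the overall model carries frailty as a covariate.

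The Participant characteristics section lists, among the variables collected at M0 and M12, "smoking, fall history, use of walking aids, experience with fall prevention interventions". Fall history is not mentioned in the analysis sections.

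**The concern.** In a randomised trial, baseline differences between arms arise by chance. Adjusting only when it seems needed therefore means choosing the model after looking at imbalance, at a shift in the coefficient, or at the result. The second half of the sentence allows stratification by modifiers that are not named, and this is separate from the planned frailty analysis, which has its own sentence. If several versions can be produced and none is designated primary, the reported estimate can be the preferred one.

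The place of frailty is also unsettled. On the Abstract's wording the main models are split by frailty; on the Methods wording there is an overall analysis plus a subgroup analysis. The headline result could be pooled without the stratum, pooled with it, or split. Splitting is costly: a trial with 80% power overall has about 51% in each of two equal halves, Φ(2.80/√2 − 1.96) = Φ(0.02).

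Fall history measures the same construct as the primary outcome and can be expected to predict it. An overall model without it, and without the stratum, gives up some precision that the baseline data could supply.

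**Working it through.** **The plan's own figure.** The Sample size section asks for 106 per group for a 50% reduction, with power 0.80 and alpha 0.05. It gives no control rate, so I assume that one third of controls fall, from the Background. For two proportions, two-sided:

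n = [1.96·√(2p̄(1−p̄)) + 0.8416·√(p₁(1−p₁)+p₂(1−p₂))]² / (p₁−p₂)²

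- p₁ = 1/3, p₂ = 1/6: 104.8, so 105 per group.
- p₁ = 0.33, p₂ = 0.165: 106.2, so 107 per group.

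The stated 106 is reproduced to within one. It matters here only because it sets the simulated size, 2 × 106 = 212 analysed.

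**Simulation of the adjustment rule.** All inputs except the size and the 1:1 allocation stratified by frailty are assumptions, because the article gives no fall rate, dispersion or covariate effects:

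- 40% pre-frail (the article aims for 30–50%), rate ratio 1.5.
- 50% with prior falls, rate ratio 2.5.
- Three weaker covariates.
- Reference rate 0.5 falls per year; mean control rate 0.5 × (0.6 + 0.4×1.5) × (0.5 + 0.5×2.5) = 1.05 before the weaker covariates.
- Overdispersed counts with dispersion 1, analysed by Poisson regression with robust standard errors.

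Type I error at a nominal two-sided 5% (4,000 runs, Monte Carlo standard error about 0.3 points):

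| Rule | Type I error |
|---|---|
| No adjustment | 5.8% |
| Frailty and fall history, fixed | 5.5% |
| Add covariates that move the estimate by more than 10% | 5.3% |
| Add covariates imbalanced at p < 0.05 | 5.4% |
| Covariate set with the largest absolute test statistic | 9.8% |

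Power (1,500 runs, Monte Carlo standard error about 1 point):

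| True rate ratio | Unadjusted | Frailty and fall history fixed |
|---|---|---|
| 0.50 | 84.1% | 86.5% |
| 0.65 | 49.1% | 52.1% |

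The gain is 2.4 and 2.9 points.

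**Analytic check on the gain.** For negative binomial counts with rate ratio 0.5, control rate μ and dispersion k, if the covariates remove a share r of the dispersion, the variance of the log rate ratio is [3/μ + 2k(1−r)]/106. Power is Φ(0.693/√variance − 1.96). With assumed μ of 0.7 or 1.2, k of 1 or 2, and r of 0.2 or 0.4:

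| μ, k | r = 0 | r = 0.2 | r = 0.4 |
|---|---|---|---|
| 0.7, 1 | 81% | 84% | 86% |
| 0.7, 2 | 70% | 74% | 79% |
| 1.2, 1 | 92% | 94% | 96% |
| 1.2, 2 | 80% | 85% | 90% |

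The direction agrees with the simulation. The size depends on r, which the article does not inform.

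**Limits.** Both calculations compare total counts. They leave out the therapist level and the time-by-treatment term, and the simulation covers adjustment only, not stratification by modifiers.

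**The case against.** The strongest reply is that this is a condensed article. Covariate lists and selection rules normally sit in an analysis plan, which is not shown and could define the condition. That answers the missing list. It does not answer the sentence itself, which states a rule for the primary analysis; a plan that named covariates unconditionally would have to replace it.

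Four stronger readings are tempting and not supported:

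- **That the trial ignores its randomisation stratum.** It does not. A frailty-stratified analysis is planned in the Abstract and the Methods, and analysis within strata conditions on the stratum. What holds is that frailty is not stated as a covariate in the overall model.
- **That fall history will be left out.** The article says it is collected and nowhere excludes it.
- **That conditional adjustment by itself inflates type I error.** Under the two mechanical rules it stayed near 5%. The investigators are also to remain blinded to allocation until the analyses are complete, which limits selection by result. The safeguard is partial: choosing the largest absolute test statistic needs no arm labels, and unless controls are also linked to a therapist, which is not stated, the therapist level would reveal the arm.
- **That a specific share of such trials would split the main result, or that power would rise from 80% to 83–90%.** Screening five modifiers at 0.10 gives 1 − 0.9⁵ = 41%, but two would give 19% and eight 57%; the article gives neither a number nor a threshold, and does not say that stratified results replace the overall estimate. The power claim holds the start at 80%, while its own inputs give 70–92% unadjusted.

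**Conclusion.** The point holds as a defect of specification. The rule as written leaves the primary estimate open, because need is undefined and no version is designated primary; the same applies to adjustment in the economic regressions. The overall model does not name the stratum used in randomisation or the M0 fall history.

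The harm to the error rate is conditional. On the assumed inputs it is about 10% against a nominal 5% if the covariate set is picked by its result, and close to nominal otherwise. The article does not commit to a mechanical rule, so it does not exclude the first case. Naming the two covariates is worth roughly 2 to 3 points of power in the simulation, a modest gain. No figure stated in the article changes.

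**What to change.** Replace the conditional sentence under Primary and secondary outcomes with wording such as:

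> The overall falls model includes frailty stratum and baseline fall history as recorded at M0, whatever the observed imbalance. Secondary-outcome models include frailty stratum and account for the M0 value once, either as an outcome time point or as a covariate. Any further adjustment is a sensitivity analysis. Frailty is the only pre-planned effect modifier, tested by interaction; any other is exploratory and does not replace the overall estimate.

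The M0 record is specified because the same characteristics are collected again at M12, after randomisation. The article gives no look-back period or count for fall history, so the covariate should follow the form in which it was recorded. The M0 value is to be used once because a time-by-treatment model may already carry it as an outcome.

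Apply the same principle to the economic regressions: frailty stratum and, where the effect measure has one, its baseline value. Then align the Abstract, the Primary and secondary outcomes section and the Economic evaluation section on whether the main estimate is overall or split by frailty.

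The cost is a little more specification work. Frailty and fall history are already collected at baseline.

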### Data collection and outcome measures

#### Primary outcome measure

The primary outcome in this study is the number of falls, with or without injuries, assessed with fall diaries and monthly follow-up telephone calls, including questions on the causes, circumstances and consequences of falls. This combination of pro- and retrospective data collection follows guidelines for conducting fall prevention trials [41].

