#### Secondary outcome measures

Besides the number of falls and fall-related injuries, positive effects on physical functioning, physical activity, quality of life and other self-reported outcome measures are measured [42]. The secondary outcome measures will be assessed at three time points during the study period; at entry of the study (baseline, M0), after 4 months to determine the short-term effects (M4) and after 12 months to determine the long-term effects (M12). Societal costs will be assessed at M4, after 8 months (M8) and M12. All secondary outcomes are listed in Table 2 and are described in detail below.

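### For falls, the stated primary effect is the time-by-treatment interaction, which on the ordinary parameterisation is not the 50% between-group reduction the trial is sized for

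*Protocol article*

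**What the plan says.** Under Primary and secondary outcomes (Statistical analysis), the article states that effectiveness "will be analysed with multilevel mixed model regression analyses for both primary and secondary outcomes". It adds: "Three hierarchical levels will be included in the mixed models; therapist, participant and time". It then fixes the quantity of interest without an exception for falls: "The primary effect in these analyses is described by the coefficient of the time treatment interaction term".

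The section on the primary outcome measure defines the endpoint as follows: "The primary outcome in this study is the number of falls, with or without injuries". The same section gives the means of collection: falls are "assessed with fall diaries and monthly follow-up telephone calls". The Abstract gives the horizon and includes injuries: "Primary outcomes are the number of falls and fall-related injuries over 12 months follow-up".

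The M0, M4 and M12 schedule appears under Secondary outcome measures and is given for those outcomes. Fall history is collected at M0 and M12, but only as one item in the list under Participant characteristics.

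The Sample size section starts from a contrast between groups: "To obtain a reduction of 50% in the number of falls between the intervention and control group". It asks for at least 106 persons per group.

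**The concern.** A time-by-treatment coefficient measures a treatment effect when the outcome has a pre-treatment value: the groups start level, and the interaction captures how far they diverge. Diary-and-call falls have no such starting value. Every count is taken after the intervention has begun, so the groups may already differ in the first period.

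The coefficient then answers another question, namely whether the relative difference grows or shrinks over the year. A programme that halved falls throughout would show no interaction. One whose benefit faded after the 14 weeks would show a positive interaction, which could be misread as an unfavourable result. The primary test and the sample size would target different quantities.

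**Working it through.** **1. What the sample size targets.** The article gives no formula and no control level, so these are attempts to recover 106 per group with two-sided alpha 0.05 and power 0.80.

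- *Two proportions.* The Background says more than one-third fall at least once a year. Assuming 1/3 against 1/6 (pooled-variance formula, no continuity correction) gives 105 per group; 0.33 against 0.165 gives 107.
- *Rate ratio.* n = (1.96 + 0.84)² × (1/μ + 1/(0.5μ) + 2k) / (ln 0.5)², with μ the control rate per year and k the dispersion. This gives 106 at, for example, μ = 0.46 with k = 0, μ = 0.67 with k = 1, or μ = 0.86 with k = 1.5.
- *Inflation.* 106 × 1.2 = 127.2, rounded up to 128; 2 × 128 = 256, as printed.

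The route used cannot be identified, but each one that lands on or near 106 sizes a plain between-group contrast with no time interaction.

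**2. What the interaction measures.** Write log(rate) = b0 + b1·time + b2·treatment + b3·time·treatment for period counts. The log rate ratio at time t is b2 + b3·t. If the ratio is 0.5 in every period, then b2 = ln 0.5 = −0.693 and b3 = 0, whatever the common time trend. On an additive scale with a constant control rate, b3 is also 0. This is algebra and needs no assumed rate.

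**3. How often each test would reject.** Monthly falls were simulated as gamma-Poisson counts with 106 per group, and fitted by log-linear regression with participant-robust standard errors (400 to 1000 trials per setting). Rates and dispersions are assumptions. The treatment effect comes from a model without the interaction.

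Constant rate ratio 0.5:

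| Falls/year, dispersion | Interaction | Treatment effect |
|---|---|---|
| 0.5, 0.5 | 5.0% | 77% |
| 0.65, 1.0 | 4.8–6.5% | 80–81% |
| 0.8, 1.0 | 6% | 87% |
| 1.0, 1.5 | 5.0–7.2% | 83–84% |
| 1.2, 1.5 | 7% | 88% |

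Using three 4-month periods instead of months gives 4.8% and 7.0% for the interaction (the 0.65 and 1.0 settings). With 400 trials, the simulation error around 5% is √(0.05 × 0.95/400) = 1.1 percentage points, so these are rejection rates of about alpha.

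Hand check of one treatment-effect figure (0.65, 1.0): variance = (3/0.65 + 2)/106 = 0.0624; SE = 0.250; 0.693/0.250 = 2.77; 2.77 − 1.96 = 0.81; power about 79%, close to the simulated 80–81%.

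Effects that change over time:

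| Pattern | Interaction | Treatment effect |
|---|---|---|
| No effect for 3 months, then 0.5 (0.5–1.0 falls/year) | 22–37% | 50–56% |
| Builds up over 3 months, then constant (0.8 falls/year) | 31% | 84% |
| Wanes from 0.3 to 0.7 (0.5–1.0 falls/year) | 19–33% | 78.5–82.5% |
| Wanes from 0.3 to 0.8 (0.8 falls/year) | 37% | 74% |

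In both waning patterns the interaction coefficient is positive, because the ratio moves back towards 1.

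**The case against.** The best defence is that the article does not give the full model. It states no link, no list of fixed effects, no coding of time, and does not say whether the response is a period count. Some specifications would make the coefficient informative. At 106 per group with a constant ratio of 0.5, rejection is 69–78% if the treatment main effect is omitted, 69–78% if the slope of cumulative falls is modelled, and 75–89% if fall history at M0 (assuming a 12-month recall) serves as time zero. A fuller protocol or analysis plan might adopt one of these.

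This stands as a limit on the claim: the zero interaction is conditional on the ordinary parameterisation and on a constant effect. A constant effect from the first month is also an idealisation, since weeks 1–4 are information and education and exercise starts in week 5. It does not rescue the sentence. None of these specifications is stated, and the choice among them moves power from about 5% to roughly 70–90%, so the primary effect cannot safely rest on it.

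Two stronger readings are tempting and not supported. A reader might infer that nothing about falls is known at baseline. In fact fall history is recorded at M0; the narrower point is that it is never designated as the baseline of the primary outcome. A reader might also infer that a single interaction coefficient forces a straight line on the secondary outcomes and so cannot give separate M4 and M12 effects. That presumes linear time, which the article does not state. With three fixed visits, categorical time is an equally ordinary reading, and the interaction suits those outcomes.

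**Conclusion.** The point holds for falls and fall-related injuries. As written, the plan names a coefficient that, on the ordinary parameterisation, does not estimate the between-group reduction in the Sample size section, and no other section defines a different effect for falls. Under a constant halving of falls the named test rejects at about its alpha level (5–7%), while the treatment effect has about 77–88% power.

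The zero expectation needs only period counts, a treatment main effect in the model and a constant ratio. The power figures also rest on assumed fall rates and dispersions, a marginal model in place of the mixed model, and omission of the therapist level. That omission can shift the power comparison but not the zero. It does not follow that the trial is bound to miss a real effect: that depends on the model finally fitted and on how the effect develops over time. The sentence should be corrected before unblinding, because it decides what the primary test tests.

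**What to change.** Amend the paragraph under Primary and secondary outcomes:

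- **Falls and fall-related injuries.** Define the primary effect as the between-group incidence rate ratio over 12 months with its 95% CI. Estimate it as the treatment coefficient, without a time-by-treatment term, in a count model that allows overdispersion (negative binomial is one suitable choice), with log follow-up time as offset and the planned therapist clustering retained.
- **Time-by-treatment for these outcomes.** Label it exploratory, as a description of whether the effect builds up or fades.
- **Outcomes measured at M0, M4 and M12.** Keep the time-by-treatment term.
- **If fall history at M0 was meant as time zero**, or another special specification was intended, the text must say so explicitly.

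The cost is one paragraph of protocol or analysis-plan wording before unblinding. No new data or participants are needed.
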